## Abstract

**Background:**

Chronic insomnia disorder (CID) is increasing in prevalence year by year, is long lasting, and potentially risky. Acupuncture has been widely used in the clinical management of this condition. However, there is still a lack of direct evidence on the dose-effect relationship between different acupuncture courses and clinical efficacy. To identify this relationship, we will design a randomized controlled trial to clarify the difference in efficacy of different acupuncture courses for CID.

**Methods and design:**

This is a prospective, parallel, single center randomized controlled trial. Two hundred and one participants with CID will be randomly divided into three groups (Group A, Group B, and Group C). The three groups will be given acupuncture therapy for 4, 6, and 8 weeks, three sessions per week, with at least 1 day between sessions. Follow-up will continue until the third month after the end of treatment. The primary outcome is the Insomnia Severity Index (ISI), and secondary outcomes include percentage of ISI < 8 points, the Pittsburgh Sleep Quality Index (PSQI), Self-Rating Anxiety Scale (SAS), Self-Rating Depression Scale (SDS), Fatigue Severity Scale (FSS), medication use, and safety.

**Discussion:**

This study is expected to provide direct evidence for the optimal treatment cycle of acupuncture for CID, as well as to facilitate health economic evaluation.

**Clinical trial registration:**

https://clinicaltrials.gov/, identifier [ChiCTR2300073711].

## Introduction

1

Insomnia is a common clinical sleep disorder that is characterized by difficulty with falling asleep, maintaining sleep, waking early, decreased sleep quality, and reduced total sleep time, accompanied by daytime dysfunction (1), such as fatigue, decreased cognitive functioning, depression/pain or irritation, and physical discomfort (2). Epidemiological data show that the incidence of persistent insomnia in the past 4 years is 76.5% (3), and patients with insomnia symptoms in developed countries such as Europe and the United States is about 30–50% (4). Approximately 10% of the adult population suffers from an insomnia disorder and another 20% experiences occasional insomnia symptoms (5). During the COVID-19 pandemic, the prevalence of insomnia is even higher (6). Insomnia is often a chronic condition, with symptoms persisting in 86% of patients 1 year after diagnosis and in 59% of patients for more than 5 years (7). CID leads to a number of consequences, such as reduced social productivity, substantial work costs and increased health care costs (8, 9), totaling more than $100 billion annually in the USA alone (10). It is evident that CID places a heavy burden on both patients and healthcare systems worldwide.

The goals of treating CID are to improve the quantity and quality of sleep, reduce the distress and anxiety associated with poor sleep, and improve daytime functioning (11). Currently, the main treatments for insomnia are cognitive behavioral therapy (CBT), hypnotic drugs, and traditional Chinese medicine (TCM) (12). However, even though CBT is recommended as a first-line, non-pharmacological therapy by international guidelines (13), it has resulted in poor patient compliance due to the different qualifications of doctors, cumbersome content, and high cost. Hypnotic drugs mainly include benzodiazepine receptor agonists, antihistamines, and other types of drugs, but there is a risk of abuse and addiction (14). Long-term use is prone to adverse effects such as drowsiness, weight gain, daytime fatigue, vertigo, delirium, ataxia, paraphilic amnesia, and sleepwalking (12), and is even significantly associated with the occurrence of serious adverse events such as traffic accidents and falls in the elderly (15, 16).

## Objectives

2

To compare the dose-effect relationship of different acupuncture courses on CID.

## Design and methods

3

### Trial design and setting

3.1

This parallel, single center randomized controlled trial will be conducted from August 1, 2023, to February 28, 2025, at the Center for Preventive Medicine, Hospital of Chengdu, University of Traditional Chinese Medicine. We will strictly adhere to the Declaration of Helsinki and the Standards for Reporting Interventions in Clinical Trials of Acupuncture (STRICTA) guidelines (29). The Ethics Committee of Hospital of Chengdu University of Traditional Chinese Medicine has approved the protocol (2023KL-064) and registration was completed in the China Clinical Trial Registry (ChiCTR2300073711). Two hundred and one participants will be randomly assigned to three groups and receive different courses of acupuncture treatments. Each participant will be made aware of the purpose of the study and the randomization procedure. Acupuncture treatment, efficacy evaluation, and medical advice were all free of charge during the observation period. The flowchart of trial procedures is shown in Figure 1.

**Figure 1 fig1:**
[figure not shown]
The flowchart of trial procedures.

### Participants

3.2

We plan to recruit participants through hospital outpatient clinics, WeChat e-posters, campuses, and communities. A researcher is responsible for screening eligible participants, and those successfully enrolled will be asked to voluntarily sign a written informed consent form (20,230,424, V2.0).

### Eligibility criteria

3.3

Participants will need to meet the following inclusion criteria: (1) meet the diagnostic criteria for CID in the International Classification of Sleep Disorders, 3rd Edition (ICSD-3) (30); (2) Insomnia Severity Index (ISI) ≥ 10 score (31); (3) Gender is not limited, age 18–70 years old; (4) have not received any acupuncture interventions in the month prior to enrollment; (5) be able to communicate normally and actively cooperate with treatment; and (6) voluntarily enrolled and had signed an informed consent form.

Those who meet any of the following criteria will be excluded: (1) combined cardiovascular, cerebrovascular, neurological, digestive, endocrine system, and other serious diseases; (2) participants with severe depression [Hamilton Depression Scale (HAMD) > 24 score]; (3) severe neuropsychiatric disorders, such as cognitive impairment, lifelong bipolar disorder, any type of schizophrenia, paranoia, dementia, organic brain dysfunction, etc.; (4) those who abuse or rely heavily on psychoactive substances such as antidepressants, central stimulants, analgesics and sedatives, and alcohol; (5) secondary insomnia caused by other organic diseases; (6) pregnant or lactating women; (7) metal allergy; and (8) participants who are enrolling in other topics.

### Randomization and blinding

3.4

Dynamic block randomization will be used to assign participants to three groups at a 1:1:1 ratio. The online central randomization system is undertaken by Chengdu CIMS Medical Technology Co. The generation of the randomized sequences will be completed by the designated investigator and participants will be given a unique number assigned by the system. Electronic data collection and data management systems will be set up by independent personnel.

The physicians responsible for the acupuncture treatments and participants in this study cannot be blinded. The data collectors, statistical analysts, and efficacy evaluators are unaware of the groupings.

### Sample size

3.5

Sample size estimation was based on the change in the primary outcome ISI score. Based on the results of existing studies in the literature, the ISI score after 4 weeks of treatment was (10.5 ± 3.8) points (32), and we expected that after 6 and 8 weeks of treatment, the ISI score would decrease by 1 point and 2.5 points. With the test level set at *α* = 0.05 and the test efficacy at 1-β = 0.9, plus calculations based on the mean comparison formula of multiple independent samples yielded 58 cases in each group. Considering a 15% dropout rate, the three groups are evenly divided at 1:1:1, with 67 cases required in each group, for a total of 201 participants are needed for this trial.

Sample size estimation formula:

$$n=\frac{\psi^{2}\left(\sum_{j=1}^{k}s_{j}^{2}/k\right)}{\sum_{j=1}^{k}{\left({\bar{X}}_{j}-\bar{\bar{X}}\right)}^{2}/\left(k-1\right)}$$

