### Statistical analysis

3.10

All statistical analysis will follow the intention-to-treat (ITT) principle, and the missing values will be supplemented by last observation carried forward (LOCF). For variables with normal distribution, one-way analysis of variance (ANOVA) will be used for comparison inter-group comparison, and paired samples *t*-test will be used for intra-group comparison. Kruskal-Wallis test will be used for non-normal distributed variables. Repeated measurements at different time points will be analyzed by using repeated-measures ANOVA. Data values will be mainly presented as the mean ± standard deviation or the median ± quartile spacing. While Chi-Square test/Fisher’s Exact test will be adopted to analyze categorical data. Categorical variables will be expressed as numbers and percentages. All statistical tests being bilateral at *p* < 0.05. Data analysis will be performed using IBM SPSS version 26.0 software (IBM Corp, New York).

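### The dropout allowance in section 3.5 adds 15% to the 58 evaluable cases instead of dividing by 0.85, so 67 per group covers about 13% dropout rather than the stated 15% (minor correction)

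*Protocol article*

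**What the plan says.** The calculation is in section 3.5 (Sample size) of the protocol article. It starts from a literature value, "the ISI score after 4 weeks of treatment was (10.5 ± 3.8) points", and an assumed gain from longer courses: "we expected that after 6 and 8 weeks of treatment, the ISI score would decrease by 1 point and 2.5 points". The design parameters are "With the test level set at *α* = 0.05 and the test efficacy at 1-β = 0.9". A formula for comparing several independent means is printed, and the article reports that "calculations based on the mean comparison formula of multiple independent samples yielded 58 cases in each group".

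The allowance for loss follows: "Considering a 15% dropout rate, the three groups are evenly divided at 1:1:1, with 67 cases required in each group". This gives the total of 201, which section 3.1 and the abstract repeat ("Two hundred and one participants with CID will be randomly divided into three groups"). The article does not write out how it went from 58 to 67.

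Section 3.10 (Statistical analysis) plans an intention-to-treat analysis in which missing values are filled by last observation carried forward (LOCF).

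**The concern.** Dropout is counted among the participants who enter the trial, so the randomized number must satisfy N × (1 − 0.15) ≥ 58. The stated 67 does not satisfy this. It matches a different operation, in which 15% of the evaluable number is added on top.

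At stake is whether the printed sample size delivers the evaluable number that the same paragraph says is needed. The 58 also carries no reserve, because it is the formula's result rounded up to the next whole number. A shortfall in the dropout step is therefore not absorbed elsewhere in the calculation.

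**Working it through.** **Inputs from section 3.5:** alpha 0.05; power 0.90; mean 10.5 and SD 3.8 at 4 weeks; decreases of 1 and 2.5 points at 6 and 8 weeks; 58 evaluable per group; 15% dropout; 67 per group; 201 in total.

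**Assumptions, because the article does not state them:**
- The SD of 3.8 applies to all three groups.
- Both decreases are measured from the 4-week value, giving means 10.5, 9.5 and 8.0.
- ψ is about 2.52. The limiting value for 2 numerator degrees of freedom, alpha 0.05 and power 0.90 computes to 2.515.

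**Step 1: reproduce the 58.** The grand mean is 28.0/3 = 9.333. The squared deviations are 1.3611 + 0.0278 + 1.7778 = 3.1667; divided by k − 1 = 2, this is 1.5833. The common variance is 3.8² = 14.44.
- ψ = 2.52: n = 6.3504 × 14.44 / 1.5833 = 57.9.
- ψ = 2.515: n = 57.7.

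Both round up to 58, so the stated figure reproduces. If the 2.5 points were taken as a further drop after the first point (means 10.5, 9.5, 7.0), the formula gives about 28 per group, which does not match. The reading used here is therefore the one behind the article's number.

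**Step 2: the dropout step.**

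| Operation | Result | Per group | Total |
|---|---|---|---|
| 58 × 1.15 | 66.7 | 67 | 201 |
| 58 / 0.85 | 68.2 | 69 | 207 |

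The article's 67 and 201 match the first row exactly. Checking back:
- 67 × 0.85 = 56.95, about 57 per group, or 171 in total against 3 × 58 = 174.
- 68 × 0.85 = 57.8, still below 58.
- 69 × 0.85 = 58.65, sufficient.
- Largest loss that leaves 58 of 67: 1 − 58/67 = 13.4%.

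**Step 3: what it costs in power.** For the omnibus F test, the noncentrality is λ = n × 3.1667 / 14.44, with 2 and 3(n − 1) degrees of freedom.

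| Evaluable per group | λ | Power |
|---|---|---|
| 57 | 12.50 | 0.891 |
| 58 | 12.72 | 0.896 |
| 59 | 12.94 | 0.902 |
| 67 (no loss) | 14.69 | 0.936 |

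Falling from 58 to 57 costs 0.8962 − 0.8906 = 0.0056, about 0.6 percentage points. Against the stated 90%, the gap at 57 is 0.9 points. About 0.4 of that (0.900 − 0.896) arises because the exact F calculation is slightly stricter than the printed formula, and it has nothing to do with dropout.

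**Step 4: scale against the inputs.** With the same formula and ψ = 2.52, an SD of 3.7 gives n = 6.3504 × 13.69 / 1.5833 = 54.9, and an SD of 3.9 gives 6.3504 × 15.21 / 1.5833 = 61.0. A change of 0.1 in the literature SD moves the required number by about 3 per group, more than the one participant at issue.

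**The case against.** The strongest reply is that the slip is immaterial. It concerns one evaluable participant per group and roughly half a point of power. The gap between 201 and 207 is 3.0% of the stated total, less than the uncertainty in the SD and in the 15% itself. This stands. It limits how serious the point is, but it does not make the sentence correct.

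A second reply is that the planned ITT analysis with LOCF keeps every randomized participant in the data set, so the analysed number would not simply fall to 57. That is also true, and 57 should be read as the number with observed outcomes. It does not rescue the arithmetic, though. Section 3.5 itself inflates for dropout and so treats dropouts as lost information. If carried-forward values were fully informative, no inflation would be needed. The 93.6% power at 67 per group would apply only if all 67 supplied real observations.

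A third reply is that the article never states its inflation rule, so multiplication by 1.15 is inferred. The inference rests on an exact match. In any case, the failure of 67 × 0.85 to reach 58 does not depend on how 67 was obtained.

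In the other direction, a reader might infer that the stated size and the stated power do not match, or that the trial is underpowered and must recruit 207. The documents do not support this: 89.1% against 90% is a negligible difference for a planning calculation.

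**Conclusion.** The sentence is wrong as written: 58 evaluable, 15% dropout and 67 randomized per group are mutually inconsistent. Either the allowance is about 13%, or about 57 per group remain at 15%. This part is pure arithmetic on the article's own figures and needs no assumption.

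The size of the consequence, about 89.1% power against 89.6% at 58 and the stated 90%, does rest on assumptions: means of 10.5, 9.5 and 8.0, a common SD of 3.8, and the omnibus F test as the sized comparison. Severity is low. The point concerns the accuracy of a reported figure and gives no reason to doubt that the trial is adequately sized for the effect it assumes.

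**What to change.** Keep 201 and restate the dropout sentence in section 3.5 in one of two ways:
- 67 per group allows for about 13% dropout from the 58 required; or
- with 15% dropout, about 57 per group remain, giving about 89% power for the omnibus test under the stated means and SD.

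The standard inflation (58/0.85, so 69 per group and 207 in total) can be shown beside it for reference. With the second wording, it is worth adding that LOCF keeps dropouts in the analysis set but does not restore the information lost with them.

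The cost is one sentence and a slightly less favourable stated figure. Recruitment, design and analysis do not change, and the total of 201 in the abstract and section 3.1 can stay.

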### Intervention

3.6

Participants in the three groups receive the same acupuncture treatments three sessions a week with at least 1 day between the two treatments: Group A (12 sessions for 4 weeks), Group B (18 sessions for 6 weeks), and Group C (24 sessions for 8 weeks). The acupoints will be selected as Baihui (GV20), Yintang (GV29), Anmian (EX-HN22, bilaterally), Shenmen (HT7, bilaterally), Neiguan (PC6, bilaterally), and Sanyinjiao (SP6, bilaterally). The localization of the acupoints refers to the national standards of the People’s Republic of China issued by the State Bureau of Technical Supervision, “Nomenclature and location of acupuncture points” (GB/T12346-2006) and “Nomenclature and location of extra points in common use” (GB/T 40997–2021). The localization of the acupuncture points is shown in Figure 2.

**Figure 2 fig2:**
[figure not shown]
① Baihui (GV20): 5 cun superior to the anterior hairline, on the anterior midline of the head. ② Yintang (GV29): At the midpoint between the medial ends of eyebrows. ③ Anmian (EX-HN22): at the midpoint between Fengchi (GB20) and Yifeng (SJ17). ④ Shenmen (HT7): On the palmar ulnar end of the transverse crease of the wrist, and on the radial aspect of the tendon of the ulnar flexor m. of the wrist. ⑤ Neiguan (PC6): 2 cun above the transverse crease of the wrist, between the tendons of m. palmaris longus and m. flexor carpi radials. ⑥ Sanyinjiao (SP6): Posterior to the mesial border of the tibia and 3 cun above the tip of the medial malleolus.

The acupuncture needles used in this study are sterile, disposable acupuncture needles (Hwato, China). Optional sizes include 0.25 mm × 25 mm (1 inch) and 0.25 mm × 40 mm (1.5 inch).

Acupuncturists are licensed TCM practitioners with at least 3 years of clinical experience. The acupuncturist determines the acupuncture points on the skin, sterilizes them with 75% alcohol, and then penetrates the skin with the acupuncture needle. All points are treated with mild reinforcing and attenuating. After Deqi (the participant feeling of “numbness, soreness, heaviness, distention”), the needle is maintained for 5 s. Specific needling requirements: GV20 (horizontal needling 0.5–1 inch), GV29 (horizontal needling 0.3–0.5 inch), EX-HN22 (perpendicular needling 0.5–1 inch), HT7 (perpendicular needling 0.3–0.5 inch), SP6 (perpendicular needling 1–1.5 inch), PC6 (perpendicular needling 0.5–1 inch). The needle is retained for 30 min, and no manipulation is done during this period. Details of acupuncture treatment are shown in Table 1.

**Table 1 tab1:** Acupuncture treatment details based on the STRICTA 2010 checklist.

Item	Item number	Detail
1. Acupuncture rationale	(1a) Style of acupuncture (e.g., Traditional Chinese Medicine, Japanese, Korean, Western medical, Five Element, ear acupuncture, etc.)	Traditional Chinese Medicine (TCM)
	(1b) Reasoning for treatment provided, based on historical context, literature sources, and/or consensus methods, with references where appropriate	The treatment is based on traditional acupuncture theory, literature search, and expert’s consensus.
	(1c) Extent to which treatment was varied	Standardized acupuncture treatment
2. Details of needling	(2a) Number of needle insertions per subject per session (mean and range where relevant)	10	(2b) Names (or location if no standard name) of points used (uni/bilateral)	Baihui (GV20/uni), Yintang (GV29/uni), Anmian (EX-HN22/bilateral), Shenmen (HT7/bilateral), Sanyinjiao (SP6/bilateral), Neiguan (PC/bilateral)	(2c) Depth of insertion, based on a specified unit of measurement, or on a particular tissue level	From 10 to 40 mm	(2d) Response sought (e.g., de qi or muscle twitch response)	Deqi (numbness, soreness, heaviness, distention, etc.)	(2e) Needle stimulation (e.g., manual, electrical)	Manual acupuncture	(2f) Needle retention time	30 min	(2g) Needle type (diameter, length, and manufacturer or material)	Sterile, disposable acupuncture needles (diameter, 0.25 mm; length, 25/40 mm; Hwato, China).
3. Treatment regimen	(3a) Number of treatment sessions	12 ~ 24 sessions	(3b) Frequency and duration of treatment sessions	Three sessions a week (at least 1 day between treatments), for 4–8 weeks.
4. Other components of treatment	(4a) Details of other interventions administered to the acupuncture group (e.g., moxibustion, cupping, herbs, exercises, lifestyle advice)	sleep medications (periodic tracking); daily lifestyle advice	(4b) Setting and context of treatment, including instructions to practitioners, and information and explanations to patients	The trial will conducted at the Center of Preventive Medicine, Hospital of Chengdu University of TCM. Two researchers will diagnose and give informed consent to the participants, the acupuncturist will be responsible for providing treatment and lifestyle advice, and two designated researchers will be responsible for randomization and data collection. All participants of acupuncture group will be arranged to the acupuncture room for treatment.
5. Practitioner background	(5) Description of participating acupuncturists (qualification or professional affiliation, years in acupuncture practice, other relevant experience)	Trained, licensed acupuncturists with at least 2 years in acupuncture clinical practice
6. Control or comparator interventions	(6a) Rationale for the control or comparator in the context of the research question, with sources that justify this choice	The acupuncture regimen is the same for each group and based on traditional acupuncture theory, literature search and expert’s consensus.	(6b) Precise description of the control or comparator. If sham acupuncture or any other type of acupuncture-like control is used, provide details as for Items 1–3 above.	All three groups will receive the same real acupuncture treatment

### Outcome measurement

3.7

Effective treatment should not only improve sleep parameters, but also produce clinically meaningful changes in daytime functioning, fatigue, anxiety, depression. Therefore, this trial will be evaluated from multiple perspectives to broaden the scope of outcome assessment (33).

#### General information

3.7.1

(1) Participant demographics: gender, age, disease duration, educational level, occupation, sleeping environment, living environment, daily living situation, personality preference, income satisfaction, marital satisfaction, exercise habits.(2) Vital signs: body temperature, heart rate, breathing, pulse, blood pressure, body mass index.

Baseline data are required to be completed within 48 h of randomization. Heart rate, pulse, and blood pressure will be assessed before and after each acupuncture treatment.

#### Primary outcome

3.7.2

##### ISI

3.7.2.1

ISI consists of seven items, with scores ranging from 0 to 4 for each item, and total scores ranging from 0 to 7 indicating normal sleep, from 8 to 14 indicating mild insomnia, from 15 to 21 indicating moderate insomnia, and from 22 to 28 indicating severe insomnia.

#### Secondary outcomes

3.7.3

##### PSQI

3.7.3.1

PSQI is used to rate the quality of a participant’s sleep in the previous month and consists of 18 items, comprising 7 components. This includes subjective sleep quality, sleep latency, sleep duration, habitual sleep efficiency, sleep disturbance, used sleep medication, and daytime dysfunction. Each component is scored from 0 to 3, and the cumulative score of each component is the PSQI total score. The total score ranges from 0 to 21, with higher scores indicating poorer sleep quality. Our prespecified primary endpoint is at the end of treatment and the secondary endpoint is 3 months after the end of treatment.

